# Enhanced Patient Activation in Cancer Care Transitions: Protocol for a Randomized Controlled Trial of a Tailored Electronic Health Intervention for Men With Prostate Cancer

**DOI:** 10.2196/11625

**Published:** 2019-03-22

**Keywords:** medical informatics, eHealth, mHealth, motivation, patient activation, prostate cancer, self-management

## Abstract

**Background:**

Prostate cancer has increased in incidence worldwide and is the leading cause of cancer death in 24 countries. The most common treatment is radical prostatectomy. However, surgery is associated with postoperative complications such as urinary incontinence and sexual dysfunction, causing decreased quality of life. If survivors are encouraged to be more active in self-care management, the symptom burden may decrease and quality of life may improve. An electronic health (eHealth) intervention based on motivational behavioral theory has been developed for this purpose.

**Objective:**

This study aimed to compare the effectiveness of standard care in combination with a tailored eHealth and mobile health self-management support system, electronic Patient Activation in Treatment at Home (ePATH), with standard care of adverse effects of prostate cancer treatment (urinary incontinence and sexual functioning) in men undergoing radical prostatectomy. The secondary aim was to test the effect on patient activation, motivation, overall well-being, and health literacy over time in and between groups.

**Methods:**

A pragmatic multicenter, block-randomized controlled trial with 2 study arms, standard care (control) and eHealth-assisted standard care (intervention), for patients undergoing radical prostatectomy. For 80% power, a sample of 242 men will need to be recruited.

**Results:**

Recruitment started in January 2018 and is expected to be completed by August 2019. Data collection will be completed in August 2020. The first cross-sectional results from this trial are anticipated to be published in January 2020.

**Conclusions:**

With the increasing number of prostate cancer survivors, attention should be paid to rehabilitation, psychosocial care, and support for endurance of self-care to reduce suffering from adverse treatment effects, poor quality of life, and depression because of postoperative complications. This project may increase knowledge of how patients can be supported to feel involved in their care and returning to as normal a life as possible. The anticipated effects of ePATH could improve health outcomes for individuals and facilitate follow-up for health care professionals.

**Trial Registration:**

International Standard Randomised Controlled Trial Number: 18055968; http://www.isrctn.com/ISRCTN18055968 (Archived by WebCite at http://www.isrctn.com/ISRCTN18055968).

**International Registered Report Identifier (IRRID):**

DERR1-10.2196/11625

## Introduction

### Background

Prostate cancer is increasing in incidence worldwide, in both developed and developing countries, and it has been ranked as the eighth most common cause of cancer death globally. A growing and aging population must be considered as a contributing factor [1]. In Sweden, over 10,000 men are diagnosed with prostate cancer every year [2]. As novel diagnostic methods and treatment approaches have significantly improved cancer survival, the number of people living with disabilities after cancer treatment is also increasing [3]. The most common treatment is radical prostatectomy (RP), which shows >95% survival 15 years postsurgery [4]. Prostate cancer survivors commonly experience long-term consequences related to adverse effects of treatment, which can reduce quality of life. Specific adverse effects following local treatment (ie, RP and high-dose radiotherapy) include urinary leakage, loss of libido, and erectile dysfunction [5-7]. Further symptoms affecting functioning in everyday life, such as psychological distress, depression, fatigue, and muscular weakness, are prevalent [8], and an increased risk of suicide is evident in the first 12 months after diagnosis [9,10]. Thus, promoting support for management of long-term physical side effects for men with prostate cancer is of utmost importance.

In 2015, the Swedish government launched a national reform to standardize cancer care pathways with the goal of speeding up cancer treatment, increasing patient involvement and satisfaction with cancer care, and reducing waiting times and regional inequalities [11]. Each patient is assigned a contact nurse who will act as a primary caregiver contact throughout the treatment period and improve care coordination, availability, and patient participation throughout the care trajectory in line with the national reform. Yet, patients have reported unmet information needs along their cancer trajectories [11-13], especially lack of information about cancer treatment and its adverse effects, as well as a need for self-management support in the aftermath of surgery [14,15].

### Adverse Effects of Prostate Cancer Treatment

Health-related quality of life in men with prostate cancer is closely associated with urinary and sexual bother and dysfunction following prostate cancer treatment. Urinary incontinence (UI; incomplete emptying, frequent dysuria, urgency, weak stream, straining, or nocturia) is common, which may affect functioning in daily life by hindering return to work and participation in social and physical activities, events, or sports [6,7]. Sexual dysfunction after prostate cancer treatment is a multifaceted problem with UI in relation to sexual activities, various orgasmic disturbances, penile shortening, and *de novo* deformity. Concerns about possible recurrence of the cancer [7] are mixed with feelings of dissatisfaction with body image, reduced physical function, emotional lability, and decreased masculine self-esteem [5]. Thus, psychological factors in relation to sexuality as well as the importance of involving the partner should be acknowledged during the rehabilitation phase [16].

### Prostate Cancer Rehabilitation

Recovery after prostate cancer treatment focuses on urinary function, sexual function, and the return to daily life. Currently, pelvic floor muscle training (PFMT) is recommended for UI following prostate cancer treatment. However, previous research shows varying effects of PFMT [17], and there is controversy regarding whether postoperative PFMT is effective for achieving urinary continence. Only 2 of 21 studies from the Cochrane review by Campbell et al (2012) [17] showed that postoperative PFMT had a statistically significant benefit. Two systematic reviews [18,19] that investigated preoperative PFMT showed inconsistent results on common side effects, including erectile dysfunction and incontinence. Chang et al [18] found evidence to suggest that preoperative PFMT improves early but not long-term continence rates. The etiology of UI after RP is multifactorial, and the mechanisms for how PFMT improves postoperative continence in men have not been fully elucidated, which may explain the inconsistent results. Furthermore, adherence to PFMT exercises and optimal frequency and number of repetitions are still sparsely studied.

Rehabilitation of sexual function is often pharmacological. However, survivors of prostate cancer are less likely to gain a proper effect from medical treatment [20]. Medical treatment is directed toward erectile dysfunction, and oral treatment with phosphodiesterase-5 inhibitors (PDE5Is) is the first-line choice. Although treatment with sildenafil (a PDE5I) is often successful, discontinuation rates for medical treatments of erectile dysfunction, including sildenafil, are found to range from 50% to 60%. Thus, a high number of men choose not to continue using the medication despite treatment being efficacious [21,22]. The current literature suggests that penile rehabilitation should start as early as possible, preferably the day after surgery. This means that PDE5Is may be most effective if treatment is initiated as soon as the diagnosis and surgery dates are confirmed [23]. However, the problem is complex, and it is likely that medication alone is simply not enough [21]. Literature shows that hypoactive sexual desire following RP occurs in 60% to 80% of men. This could partly be because of a psychological impact of the cancer on mental health and body image [24]. Although there is a place for medical and surgical therapies in erectile function recovery and or preservation, psychological and sexual counseling may be equally important in sexual rehabilitation after RP [24]. Therefore, alternatives such as sexual therapy techniques (sexual communication and stimulation) have been suggested [25].

Exercise is increasingly seen as significant in prostate cancer rehabilitation as a strategy to enhance sexual function as well as improve feelings of masculinity and reduce the distress men experience after prostate cancer [26]. The national recommendations on physical activity in cancer are 20 min of endurance training daily, along with aerobic training or household work 1 hour per week [27]. A meta-analysis [28] shows that introducing exercise in the rehabilitation may reduce the loss of muscle mass, fatigue, and psychological morbidity that may arise from cancer treatment. First-degree evidence shows that exercise improves quality of life, fatigue, and body strength. A systematic meta-review suggests that exercise also has an effect on incontinence in men with prostate cancer [29], and PFMT together with exercise might have a positive effect on sexual activity [28,30]. Altogether, there is a growing body of literature suggesting that single interventions are not enough to address the complexity of adverse effects of prostate cancer treatment. Rather, a combination of multiple interventions, including PFMT, exercise, cognitive behavioral therapy, psychoeducation, and peer support, is suggested to be the most effective in decreasing distress and improving health-related quality of life [28,30,31].

### Web-Based and Mobile Electronic Health Apps

Electronic health (eHealth), referring to health services delivered or enhanced through the internet and related technologies [32], has the potential to meet patients’ needs for tailored information and provide person-centered self-management support and encouragement for sustained healthy behaviors [33]. Increasingly, medical and public health practices are supported by mobile devices (mobile health, mHealth) that allow for bidirectional communication or on-demand access to health services, extending the accessibility of support beyond temporal and physical boundaries [34,35]. Despite the opportunities provided by mHealth apps for remote support and communication and an abundance of apps on the market, only a few apps focus on supporting patients during cancer treatment and follow-up [36]. Existing studies suffer from poorly validated information, and there is still a lack of rigorous trials regarding quality of life and postoperative rehabilitation in prostate cancer. Ongoing studies in Canada [37], the United Kingdom [38], and Sweden [39] explore the effects on early detection or follow-up care of introducing e & mHealth prostate cancer care with a focus on increased patient participation and interaction. However, different theoretical frameworks and intervention strategies are used to approach this goal.

This protocol describes the third phase of the electronic Patient Activation in Treatment at Home (ePATH) project, which started in 2015, targeting the care trajectory of cancer patients. The first phase explored prostate cancer patients’ need for support, during cancer treatment and follow-up, that facilitates self-management activities and a proactive interaction with health care professionals [14]. The second phase encompassed development of the content and functionality of the eHealth- and mHealth-assisted self-management support system, ePATH, by applying user-centered design, testing and optimizing in iterative cycles to satisfy patient requirements, and adapt to the context [40,41].

The aim of the third phase was to compare the effectiveness of a tailored eHealth- and mHealth-assisted self-management support as a complement to standard care, with standard care. Primary outcomes are postoperative adverse effects (ie, urinary and sexual bother and function) in men undergoing RP. The secondary outcomes are physical activity, patient activation, motivation, health literacy, and overall well-being, which may be associated with the primary outcomes and have a mediating or confounding effect on the intervention.

The hypotheses of the study are the following:

The ePATH self-management support system will have a greater effect than standard care on patient-reported outcomes of UI and sexual bother and function at 1, 3, 6, and 12 months after RP.The ePATH self-management support system will have a greater effect than standard care on (1) physical activity, (2) patient activation, (3) motivation, (4) health literacy, (5) overall health and well-being, and (6) endurance and adherence to self-care at 1, 3, 6, and 12 months after RP.

## Methods

### Design

This protocol describes a pragmatic multicenter block-randomized controlled trial with 2 study arms for patients undergoing RP: standard care (control arm) compared with standard care in combination with the ePATH self-management support system (intervention). A pragmatic trial design has been chosen to test whether the intervention (ePATH) works under normal conditions in routine clinical practice [42]. The protocol conforms to Standard Protocol Items: Recommendations for Interventional Trials guidelines (Table 1).

### Participants

All men diagnosed with prostate cancer at the study sites in Southeast Sweden where the chosen treatment is RP (open, laparoscopic, or robot-assisted) will be eligible. Inclusion criteria include being able to speak, read, and understand Swedish, having or being able to get a mobile BankID (the leading solution for electronic identification used in Sweden) for safe handling of personal information, having access to an email address, and being computer literate.

### Recruitment

Consecutive recruitment of patients will take place at 3 surgical and urology clinics in southeast Sweden*.* Eligible patients are to be identified by the contact nurses at the 3 study sites. In this study, the contact nurses will act as the communication channel among the researchers, the clinics, and the patients. The patients will receive both verbal and written information about the study in conjunction with diagnosis. Within 1 to 2 weeks, the contact nurses will contact each patient and ask about interest in participating in the study, and those who volunteer will submit their written consent form to the contact nurse (site B) or send their written consent in a prestamped, addressed envelope to 1 of the researchers (AH; site A and C; Figure 1). The researcher (AH) will send the Web-based baseline questionnaire to the patients. Afterward, the patients will be randomized to the 2 study arms. Patients randomized to the intervention group will receive an email informing them that an account has been created in ePATH. Patients randomized to the control group will receive an email telling them that no account has been set up (Figure 1). Due to the nature of the intervention, blinding of contact nurses or patients is not possible. None of the researchers are involved in patient care.

**Table 1 table1:** Overview of timepoints, enrollment and assessments.

Study period		Timepoint						
		Enrollment: 4 weeks pre-RP^a^	Baseline: 2 weeks pre-RP	Discharge: 3-7 days post RP	Follow-up			
					1 month	3 months	6 months	12 months
**Enrollment**								
	Eligibility criteria: speak, read, and understand Swedish; Active email address; Planned RP surgery; Computer literacy; Access to computer, tablet, and mobile phone; Mobile BankID, or willing to apply for mobile BankID	X^b^	—^c^	—	—	—	—	—
	Information about the study	X	—	—	—	—	—	—
	Informed consent (written)	—	X	—	—	—	—	—
	Allocation: cluster randomization; Intervention: standard care+ePATH^d^; Control: standard care	—	X	—	—	—	—	—
	Journal data: cancer severity, length of hospital stay, type of surgery, postoperative complications	—	—	T_0_^e^	—	—	—	—
**Assessment**								
	Demographic data	—	T_0_	—	—	—	—	—
	Expanded Prostate Cancer Index Composite	—	T_0_	—	T_1_	T_2_	T_3_	T_4_
	Pelvic floor muscle training	—	—	—	T_0_	T_1_	T_2_	T_3_
	Physical rehabilitation	—	—	—	T_0_	T_1_	T_2_	T_3_
	Physical activity (SGPALS^f^)	—	T_0_	—	T_1_	T_2_	T_3_	T_4_
	Sexual rehabilitation	—	—	—	T_0_	T_1_	T_2_	T_3_
	Patient Health Questionnaire	—	T_0_	—	—	T_1_	T_2_	T_3_
	Needs Satisfaction Frustration Scale	—	T_0_	—	—	—	T_1_	T_2_
	Patient Activation Measure	—	T_0_	—	—	T_1_	T_2_	T_2_
	Cancer Behavior Inventory	—	T_0_	—	—	T_1_	T_2_	T_3_
	General health (RAND-1^g^)	—	T_0_	—	T_1_	T_2_	T_3_	T_4_
	Sleep Condition Indicator (short version)	—	T_0_	—	—	T_1_	T_2_	T_3_
	Fatigue Severity Scale	—	T_0_	—	—	T_1_	T_2_	T_3_
	Communicative and critical health literacy	—	T_0_	—	—	—	T_1_	T_2_
	Total questionnaire items	—	67	—	33	53	71	77

^a^RP: radical prostatectomy.

^b^X: procedure will be done.

^c^Not applicable.

^d^ePATH: electronic Patient Activation in Treatment at Home.

^e^T_0…4_: Time point for baseline (=0) or follow-up (=1-4) assessment.

^f^SGPALS: Saltin-Grimby Physical Activity Level Scale.

^g^RAND-1: 1 item from Veteran’s RAND 12-Item Health survey.

**Figure 1 figure1:**
[figure not shown]
The CONSORT diagram shows how patients’ recruitment and flow through the randomized trial of two groups including attrition rate will be reported. (n) denotes the number of patients included and lost at each step.

### Sample Size

Considering an effect size of 0.5 and a maximum of 4 domains (urinary, bowel, sexual, and hormonal) on the Expanded Prostate Cancer Index Composite with a 2-sided 5% significance level and a power of 80%, a sample size of 121 patients per group will be necessary given an anticipated dropout rate of 25% [43].

### Randomization

A computer-generated block randomization list will be produced by an independent statistician, who is not involved in the trial, to allocate participants to the 2 study arms. The statistician will retain information about block sizes and the randomization list for the duration of the study. The order will be concealed from the researchers through the use of sequentially numbered, opaque, sealed envelopes. The envelopes will be opened consecutively by 1 of the researchers ([name]) when patients have been included and allocated to the study arms. The researchers involved in the study will be blinded to block sizes.

### The Electronic Patient Activation in Treatment at Home Intervention

ePATH is conceptually based on a theoretical framework, self-determination theory [44], and the assumption that promoting autonomy, competence, and relatedness are factors that foster intrinsic motivation and engagement in sustained self-management. Patient activation in self-care entails understanding one’s own role in the care process, having the knowledge, skills, and confidence to perform the required behaviors [45], and creating the social support necessary for the initiation and maintenance of the desired behavior [44,46]. In ePATH, autonomy is supported by an engaged patient-nurse interaction, enabling patients to make a selection of self-care activities. Relatedness is supported through the message function, which will enable a 2-way communication with the contact nurse. Support for autonomy, competence, and relatedness in ePATH is expected to enhance patients’ motivation to engage in self-care.

ePATH is developed as a Web-based tool and also comprises a mobile app for mobile phones. The system makes use of national services for safe authentication for citizens (mobile BankID) and health care staff (e-legitimation, SITHS). ePATH provides access to tailored comprehensive information about diagnosis and treatment, a rationale as to why self-care is needed, health care contacts, a list of medications, and, finally, a set of self-care activities, with self-selected goals and ratings related to the activities.

ePATH contains functionality, enabling the patient to communicate with his or her health care contacts, report self-care activities (eg, PFMT or physical exercise), symptoms of relevance for diagnosis (eg, UI, sexual bother and functioning, distress, and fatigue), and follow-up on reported data over time. Notifications to exercise or take medication can be activated to provide the patient with support and reminders.

Self-care activities in ePATH focus on PFMT, psychosexual self-management, and exercise, as these activities are directed at the main symptoms after surgery. Self-care activities for UI include PFMT in the form of Kegel exercises (ie, contraction and relaxation of the pelvic floor muscles) 3 times per day to increase strength. A suggested physical exercise program including endurance training (jogging, running, etc) and resistance training (weight lifting, sit-ups, planks, etc) will be available. The intensity of exercise is determined based on the physical condition of the patient and can be assessed by the patient using the revolutions per minute Borg scale in the app; examples of suitable activities have been developed in collaboration with a physiotherapist [47-48]. For most men, sexual function is affected by the surgery. To increase the patients’ understanding of the postoperative situation and rehabilitation options, ePATH provides information about medical treatments and self-care activities for the sexual rehabilitation. There is also a diary function, where the men can write down their feelings, experiences, and thoughts related to sexual bother and function.

### Intervention Group

The intervention group is treated in accordance with the standard guidelines for RP at the clinic and the group has access to the ePATH self-management support system. Information about ePATH and how to navigate the app is provided in a written pamphlet. For those participants who so wish, a face-to-face meeting with the contact nurse or researcher may be arranged for practical guidance and training. Contact nurses at each of the 3 study sites have likewise been trained in how to navigate in the ePATH as well as in the protocol to ensure standardized follow-up.

At inclusion, the contact nurse and the patient review self-care activities and tailored goals of self-care. Patients have the possibility to evaluate and adjust goals and activities during the care trajectory through the message function in ePATH, over the phone, or in person during follow-up visits. Furthermore, the nurses check that patients are aware of the functions of ePATH: how to send messages, register activities performed and medications taken, make notes, and activate reminders.

### Control Group

Men randomized to the control group receive standard care following RP, with verbal and written information about PFMT (Kegel exercises), the diagnosis, the surgical procedure, and symptoms related to treatment (ie, urinary symptoms and affected sexual function). Follow-ups after discharge are in accordance with normal procedures at the clinics, with visits to an urotherapist or sexologist, a contact nurse, and a surgeon. As study sites are located in different counties, standard care is organized differently at each site (Figure 2).

### Outcome Measures

Participants in both study arms are asked to complete questionnaires at baseline and at 1, 3, 6, and 12 months after surgery. The contact nurses extract information on cancer severity (Gleason score), surgical procedure (open, laparoscopic, or robot-assisted), length of hospital stay, and possible postoperative complications that affected discharge from the patients’ medical records. A detailed time schedule of assessments and questionnaires is presented in Table 1.

At baseline, sociodemographic questions about age, marital status, educational level, and household income are included.

Primary outcomes are patients’ urinary and sexual bother and function, measured by use of the Expanded Prostate Cancer Index Composite-26 item, which contains 26 items to measure patient function and bother after prostate cancer treatment in urinary, bowel, sexual, and hormonal domains. Higher scores represent better health-related quality of life [43]. A total of 2 items concerning frequency of performed PFMT and support of sexual rehabilitation will also be included. See Textbox 1 for secondary outcomes.

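### The stated 80% power is for one of four EPIC domains at one unnamed time point at an implied 1.25% level, so it does not describe the test of hypothesis 1

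*Protocol article*

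**What the plan says.** The places that define the primary question differ in outcomes, visits and test level.

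- **Outcome Measures:** the primary outcomes are "urinary and sexual bother and function, measured by use of the Expanded Prostate Cancer Index Composite-26 item". The aim in the Introduction agrees.
- **Abstract, Objective:** a shorter form, "adverse effects of prostate cancer treatment (urinary incontinence and sexual functioning"), which leaves out bother.
- **Hypothesis 1 (end of the Introduction):** a greater effect than standard care on "UI and sexual bother and function at 1, 3, 6, and 12 months". No visit is singled out. Nothing says whether one, some or all comparisons must be positive.
- **Sample Size:** an effect size of 0.5 and "a maximum of 4 domains (urinary, bowel, sexual, and hormonal) on the Expanded Prostate Cancer Index Composite", two-sided 5%, 80% power, 25% dropout, giving 121 per group (242 in the Abstract). It names no visit and does not say how the four domains enter the calculation.
- **Analysis:** repeated-measures models over the four visits for the primary outcomes, with a two-sided 5% level for every test and no division over domains or visits.

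**The concern.** A power figure means something only when tied to a defined test: which outcome, which time point, which alpha, and what counts as success. Here the sample size uses a wider set of domains than the primary outcomes and no visit. The hypothesis spans four visits, and the analysis applies a different alpha from the one the sample size implies.

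At stake is what a positive result would mean. If one significant comparison is enough, the overall false-positive risk is well above 5%. If every comparison is needed, power is below 80%. The document does not say which applies, and the outcomes are patient-reported in a trial where patients cannot be blinded.

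**Working it through.** **Inputs.** From Sample Size: d = 0.5, power 80%, two-sided 5%, 25% dropout, 121 per group. From hypothesis 1: four visits. From Outcome Measures: urinary and sexual, function and bother. From Analysis: 5% per test. Assumed, because the document gives none: correlation 0.2–0.5 between domains and 0.5–0.8 between visits, with d = 0.5 at every visit.

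**1. Reproducing 121 per group.** For two means, n per arm = 2(z₁₋α/₂ + z₀.₈₀)²/d². At α = 0.05/4 = 0.0125 this is 2(2.498 + 0.842)²/0.25 = 89.2. The t-test version is 90.78, and 90.78/0.75 = 121.04, the stated figure. Other splits (t-test version):

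| Tests sharing alpha | α each | n per arm | after 25% dropout |
|---|---|---|---|
| 1 | 0.05 | 63.8 | 85 |
| 2 | 0.025 | 77.3 | 103 |
| 4 | 0.0125 | 90.8 | 121 |
| 8 | 0.00625 | 104.2 | 139 |

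Only the four-way split matches.

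**2. What the planned number delivers per test.** Evaluable per arm: 121 × 0.75 = 90.75. Two-sample t-test power at d = 0.5 is 80.0% at α = 0.0125, 86.5% at 0.025 and 91.8% at 0.05. So the stated 80% belongs to one domain at one time point at 0.0125. At the level the Analysis section states, the same comparison has about 92%.

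**3. Size of the family in hypothesis 1.** Two domains × four visits = 8 comparisons. Counting function and bother separately gives 16.

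**4. Consequences at 5% per test, for the eight comparisons.** Treat the eight test statistics as correlated normals with critical value 1.960. Their mean is 0 under no effect and 0.5 × √(90.75/2) = 3.368 under the planned effect. The correlation between different domains at different visits was set in two ways: as the product of the two assumed correlations, or equal to the between-domain one. By simulation, over both:

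- Any one of eight significant when there is no effect: about 20–28%. Under independence it would be 1 − 0.95⁸ = 34%. These are two-sided figures, so about half of such errors would favour ePATH.
- All eight significant under the planned effect: about 63–75%. Under independence it would be 0.92⁸ = 51%.
- Both domains at one visit: about 85–86%.

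**5. Whether the trial is too small.** Two domains at one visit at 0.025 each need 103 per arm, against 121 planned. One test per domain of the four-visit average has mean statistic 3.368/√((1 + 3r)/4). That is 4.26 at r = 0.5 and 3.65 at r = 0.8, giving power of 96% and 88% even at 0.0125.

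**The case against.** The strongest reply is that the sample size is, if anything, generous. Urinary and sexual are among the four domains and the text says a maximum of four, so counting bowel and hormonal makes the number conservative for two primary domains. A four-way split is also what urinary and sexual, each with function and bother, would need at one visit. Repeated-measures models could supply a single across-visit test per outcome, and an unseen analysis plan may fix the visit and the multiplicity rule. All of this stands against any claim that the trial is underpowered. It does not answer the point that the article states the outcome set and the alpha in incompatible ways. Those are statements on the page, not details left out.

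Stronger readings that a reader might infer, and why the document does not support them:

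- *The trial was sized on the wrong outcomes.* Both primary domains are in the list. Only bowel and hormonal are extra, and EPIC-26 collects them anyway.
- *Power falls to 67–70% for both domains at one visit, or 35–51% at all four.* Those figures test each comparison at 0.0125 and also require all to succeed. The protocol states no such success rule, and a rule of that kind needs no alpha split.
- *Incontinence is misdefined as an endpoint.* The parenthesis "Urinary incontinence (UI; incomplete emptying, frequent dysuria, urgency, weak stream, straining, or nocturia") is loose background text that omits leakage. The measured outcome is the EPIC-26 urinary content, and the power argument does not depend on this wording.
- *The outcome will be picked after the fact.* The wording leaves room for that, but nothing shows intent.

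**Conclusion.** The point holds as an inconsistency in the plan, not as a shortage of patients. The 80% is the power for one EPIC domain at one unnamed time point at 0.0125, and neither the outcome set, the visits nor the alpha matches hypothesis 1 and its analysis. Depending on how hypothesis 1 is read, the plan as written gives a familywise error of about 20–28% (any one of eight comparisons) or joint power of about 63–75% (all eight).

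The four-way split is inferred, since it is the only one tried that returns 121. The ranges depend on the assumed correlations and on d = 0.5 holding at every visit. The per-test powers and the 103 per arm do not depend on the correlations. The matter should be corrected because it changes what the trial may conclude.

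**What to change.** - State the primary family in the same words in the Abstract objective, the aim and hypothesis 1, Sample Size and Outcome Measures.
- Name one primary visit, or one overall across-visit test per outcome, and make the other visits secondary.
- Use the same alpha split in Sample Size and Analysis.

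The sample-size sentence then follows from the family chosen, here with one primary visit:

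- **Urinary and sexual domain scores:** drop bowel and hormonal, and state that 121 per group gives about 86% power per domain at alpha 0.025, d = 0.5 and 25% dropout.
- **Function and bother kept as four primary outcomes:** keep alpha 0.0125 and 80% per outcome, and name those four in place of the four domains.

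The sponsor chooses the family and the visit. Demoting bother or fixing 12 months is not required by this point.

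The cost is protocol and analysis-plan wording and a registry update, with no additional patients. Recruitment began in January 2018, so the change redefines primary endpoints in a running trial. It should be dated, documented and made before any comparative data are seen.
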